#### Verbal stimulation

It is anticipated that verbal stimulation will increase participants’ motivation to undertake physical activity. Presented herein is a model physical exercise program that incorporates the use of verbal stimulation. The model is focused on the study participant’s achievement of (objective) functional goals, and altering their (subjective) perception of the intensity of the training program and individual aims. According to the Competence-based Models of Intrinsic Motivations Theory [28], the efficiency of motivation depends on the person’s conviction of the significance of the set goals.

During baseline assessment, the objectives of exercise participation – both short- and long-term – will be defined. Short-term refers to what a person can do within daily exercises (e.g., perform 20 sit-ups to increase the strength of the lower limbs), whereas long-term objectives concern the “ultimate goal” (e.g., improved mobility, ability of unassisted walking to the grocery). Specified objectives will allow individuals to strive to achieve the goals and thus help them to persevere in their new health behaviors [29]. During the exercise program, progress in achieving functional goals will be analyzed. In accordance with the results of the research by Park et al., [30] determining functional objectives is an important motivation factor for older people to take up physical activity. Moreover, Resnick et al. [31] stated that defining the goals of functional activity, along with achieving and evaluating them, influences the improvement of functional status and increased involvement in physical activity.

The verbal stimulation program, which considers the individual tasks related to the physical exercises, will be adapted to the long-term objectives identified at baseline assessment.

Exercises conducted during classes will be focused on short-term objectives and, prospectively, on achieving the main (long-term) goal.

The verbal stimulation model to be implemented in the presented study is based on the research of Park et al. [30], and will include the following:An assessment of the study participant’s perception of their own performance of the functional activity; specifically, whether the participant perceives their starting position, movement, and final position to have followed the correct motion pattern. The participant will be asked: “Do you feel that you performed your task well?” The question is intended to increase internal motivationA qualitative assessment of task performance will consist of the study participant determining the goal of the activity, and answering the question: “Is the quality of the task you fulfilled, good?” This question is intended to increase internal motivation by connecting their achievement with satisfactionAn assessment of the perception of one’s (the study participant’s) own functional activity in accordance with their capability of performing specific tasks. The process will consist of determining the degree of difficulty of the task and evaluating whether performance of the task, despite the degree of difficulty, is feasible. If a task is found to be infeasible, it will be divided into simpler parts. Gradation of difficulty will allow the execution of the task and should allow the participant to generate a more positive association with the activity, helping to eliminate anxiety related to undertaking exercise [32]Provision of support for group members. Each group will be encouraged to focus on one purpose: to increase the functional activity of themselves and each other

According to Locke, raising an older person’s need for physical activity may be achieved by increasing awareness of the motion aspects of human movement and discussing anxieties associated with undertaking physical activity [33].

During the exercise program, physiotherapists will discuss any unpleasant sensations associated with the exercise. Older people will be provided with information explaining how they can reduce pain associated with the activity, if experienced (e.g., hot/cold compresses). Seniors will also be guided as to how to develop a realistic attitude toward the adverse effects of intensified exercises (e.g., muscle pain will not cause further damage to bones or joints).

Verbal stimulation is meant to provide positive stimulation to achieve the success associated with the activity and to overcome any fear of the activity [34].

The verbal stimulation program will be included in the individual exercise programs. The physical exercise programs will be carried out by physiotherapists (one therapist at the nursing home) with at least 2 years of experience in exercise training of older people. Each of the therapists will be trained in exercise programs and verbal stimulation before the start of the program. The intervention will be considered complete if the participant attends at least 80% of the sessions [35, 36]. Therapists will take charge of logging and assessing the attendance of older people at the exercise programs.

The interventions described above involve low risk in relation to health and life. For the duration of the examination, each of the leading therapists will monitor the somatic symptoms of the participants, and determine which directly result from the intervention. Each incident will be dealt with individually and recorded in the protocol of adverse events. In the event of health problems, such as pain or malaise caused by excessive effort, the physician supervising the study will decide on participant exclusion.

During the trial, patients will be advised not to take part in the other group physical activities. Monitoring activities will be conducted therapists responsible for group exercises in the nursing home.

### Outcome measures

Sociodemographic information will be collected and will include age, gender, Body Mass Index, marital status, education level, and time spent in residential care. Depressive symptoms of potential study participants will be measured using the GDS [37], version 15 (GDS-15) [38]. Cognitive function will be evaluated, and potential cognitive impairment identified, using the 30-item MMSE [39].

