### Recruitment

Selected care homes for older people and the chronically physically ill in Southeast Poland will be included in the study. The group of ten nursing homes will be randomly selected. In the case of an insufficient number of participants, another draw will be conducted and the previously chosen residential home will be excluded. Management centers will be informed about the purpose and conduct of the study. After obtaining approval for the project, each center will begin recruiting participants and promotional activities. Pre-qualification for participation in the study will be carried out by a physiotherapist working in the center. A physician employed in a nursing home, after consultation with the research team, will be required to give express written consent to the participation of selected older people in the project, taking into account lack of contraindications to physical exercise. After obtaining written permission from the physician for inclusion in the program, the consent of the study participants prior to baseline assessment will be obtained.

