### Participants

Participants eligible for the trial must comply with the following criteria at randomization:Residents of care homes for older people and people with chronic illnessesAged 65–85 yearsMini-Mental State Examination (MMSE) score > 19Geriatric Depression Scale (GDS) score < 20 pktSpend free time sitting at least 4 h/day, 6 to 7 days/week (Physical Activity Scale for the Elderly (PASE))

Exclusion criteria:Severe systemic diseaseSevere circulatory or organic insufficiencySevere neurological disorderLack of consent by the older person or their physician

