### Sample size

An a-priori power analysis was conducted to determine the sample size necessary to find statistically significant exercise effects [52]. The sample size calculation is based on the primary outcome and analysis. The sample size was chosen according to the Cohen method, using standard assumptions: 0.05 for significance level, 0.8 for power of test, 0.5 for effect size which accounts, according to Cohen, for medium effect size. For the final analysis, the total participant number will be 156 (39 in each arm). To allow for a 25% dropout rate, 208 senior participants will be recruited.

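### The depression entry limit (GDS below 20) and the version named for screening (GDS-15) do not share a score range, so the criterion as written cannot exclude anyone

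*Protocol article*

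**What the plan says.** In the protocol article, the eligibility list under Participants opens with "Participants eligible for the trial must comply with the following criteria at randomization". One entry is a GDS score below 20 points. The list does not say which version of the scale is meant.

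The version appears under Outcome measures: "Depressive symptoms of potential study participants will be measured using the GDS [37], version 15 (GDS-15) [38". The sentence refers to potential participants, that is, residents being screened. The next sentence in that section covers the Mini-Mental State Examination (MMSE), the other screening scale in the eligibility list. No other GDS version is named anywhere in the article, and no scoring range for the scale is given.

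Nothing else in the eligibility rules deals with depression. The exclusions cover serious systemic, circulatory or organ, and neurological disease, and missing consent. Under Recruitment, the physician's written approval is given "taking into account lack of contraindications to physical exercise", which is a different question.

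**The concern.** A numerical entry limit acts only if the instrument can return scores on both sides of it. Here the limit appears to belong to a longer scale than the one named. If staff follow both sections literally, every resident passes, including one who endorses all 15 items.

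The sponsor chose to restrict entry on depressive symptoms, and there is reason to care whether that restriction works. The verbal stimulation component is aimed at motivation, completion is defined by attendance at 80% or more of sessions, and the outcomes include self-reported activity (PASE) and the mental domains of the SF-36. It is reasonable to expect marked depressive symptoms to bear on these. A reader of the eligibility list would take the results to apply to residents screened for depression.

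There is also a practical risk. Pre-qualification is done locally, in ten randomly selected homes. If some homes applied the rule literally and others substituted another version or limit, eligibility would differ between homes.

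**Working it through.** The limit of 20 is a stated value with no derivation, so there is no figure to reproduce. The check compares the range of possible scores with the limit.

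**Inputs**
- Limit: score below 20, applied at randomization (Participants).
- Instrument: "version 15 (GDS-15"), used on potential participants (Outcome measures).
- Points per item: 1. This is an assumption taken from the version name; the article prints no scoring range.

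**Step 1. Range of the named version.** Maximum = 15 items × 1 point = 15. Possible scores are 0 to 15, which is 16 values.

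**Step 2. Scores the limit removes.** A resident is excluded only at 20 or more. Since 15 < 20, this removes 0 of 16 values. The gap between the highest possible score and the limit is 20 − 15 = 5 points.

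**Step 3. How far the assumption would have to fail.** For a 15-item sum to reach 20, the items would have to average at least 20/15 = 1.33 points each. One point per item cannot give this.

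**Step 4. Comparison with a longer scale.** For a hypothetical 30-item version at one point per item (assumption), the scores run from 0 to 30, which is 31 values. The limit would remove scores 20 to 30, which is 11 of 31 values. A limit of 20 can therefore act on a scale of that length, but not on the version named.

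**Step 5. Comparison with the other screening scale.** The article describes the MMSE as having 30 items and requires a score above 19. On a 0 to 30 range (assumption: one point per item) that limit lies inside the scale and removes scores 0 to 19. Of the two screening scales for which the article gives both a form and a limit, only the GDS has a mismatch.

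**Step 6. Could another rule restore the screen?** None of the exclusion criteria names depression, and the physician's approval concerns fitness for exercise. As written, nothing else does the work of the GDS criterion.

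**The case against.** The strongest reply is that this is a slip in a condensed article. The eligibility list names no version, the Outcome measures sentence cites the general scale and the 15-item version as separate sources, and the full protocol and screening form are not shown. If the version is the slip, a longer scale may have been used and the screen may have worked. This stands as a limit on what can be said about practice. It does not remove the point: the article states both the limit and the instrument, the two do not fit, and it does not show which entry is wrong.

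A reader might infer more than the documents support, in four ways:

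- **That the enrolled population breaches the protocol.** It does not. Everyone enrolled on the GDS-15 would satisfy the written limit. The supportable statement is that the limit does not restrict entry on depressive symptoms.
- **That the criterion has in fact excluded nobody.** This presumes that every home used the GDS-15 with a limit of 20, which the article does not establish.
- **That severely depressed residents have entered.** A limit that cannot act means only that they are not excluded by score. Entry still requires pre-qualification by a physiotherapist, the physician's written approval, the resident's own consent and an MMSE score above 19. None of these is a depression criterion, but the documents do not show who passed them.
- **That the dropout allowance is therefore wrong.** The Sample size section gives no rationale for its 25% and does not tie it to a population screened for depression. Its arithmetic is sound: 156/(1 − 0.25) = 208.

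**Conclusion.** The mismatch holds with high confidence. On the named version the limit removes 0 of 16 possible scores, and it is the only depression criterion in the article. The one assumption is one point per item, which the version name implies but the article does not state.

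The consequence is limited to who may be enrolled and to whom the results can be generalised. Randomization protects the comparison between arms, and neither the alpha level nor the sample-size calculation depends on this criterion. No numerical effect on the results can be derived from the documents. This is an internal inconsistency that should be corrected; it does not threaten the validity of the trial.

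**What to change.** 1. Reconcile the Participants and Outcome measures sections so that the GDS version and the limit belong to the same score range, and name the version in the eligibility list. The choice of version and value is for the sponsor and its clinicians.
2. Apply the reconciled criterion to any further recruitment. The Trial status section says recruitment was open at submission; whether it still is cannot be seen from the article.
3. Keep all residents already randomized in the intention-to-treat (ITT) set.
4. Report baseline GDS by arm, and the version and limit actually used at screening, by home if they differed.
5. If the GDS-15 is kept, add one sensitivity analysis of the SPPB restricted to residents who meet the reconciled limit at baseline. If a longer version is chosen, residents already measured with the GDS-15 have no score on it, and this analysis cannot be run for them.

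The cost is a short amendment to the text, a reporting item and, if the GDS-15 is kept, one further analysis of data already held. The small downside is that slightly fewer residents may be eligible from then on.

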### Main outcome

The Short Physical Performance Battery (SPPB) is used to evaluate physical fitness [40]. Function of the lower limbs will be assessed using: (1) static balance, (2) gait speed, and (3) getting up from a chair. Each of the elements will be scored from 0 to 4. The final result will be the sum of the points from three attempts.To assess static equilibrium, the participant will perform three stands (side-by-side, semi-tandem, and tandem positions) and hold the position for 10 sTo assess gait, participants will be asked to walk a distance of 3 mTo assess the strength of the lower limbs, the participant will perform the task five times, without using their hands. The total execution time will be recorded

Data will be collected at the following time points: at baseline (before commencement of the intervention), immediately after completion of the intervention, and 12 and 24 weeks after the completion of the intervention.

### Secondary outcomes

The Physical Activity Scale for the Elderly (PASE) is used for the assessment of physical activity of people over the age of 65 years [41]. It includes an evaluation of the way that free time is spent, and the work-related activities or volunteer work conducted within the 7 days prior to the execution of the survey. The scale consists of 12 questions evaluating the frequency and duration of activity that the participant has partaken in during this time (for example, walks, exercise, housework, gardening, and caring for others) [42]. The overall scoring scale is from 0 to 793, with higher scores indicating a higher level of physical activity. Within the framework of the planned research, validation of the Polish version of PASE will be conducted.

The Timed Up and Go (TUG) test [43] is quick, and is widely used in clinical practice for the initial evaluation of the functional capabilities and balance of older people. The TUG test will be performed as follows: the participant will stand (from a sitting position on a chair), walk a distance of 3 m, turn around (180°), walk the 3 m back to the starting position, and resume the sitting position. The final result will be the average time of three attempts. A cognitive element will be introduced in a second test; specifically, the participant will perform the TUG test while attempting to count backwards, in sets of three, from a number determined by the examiner. A TUG score of ≥13.5 s and TUG cog ≥ 15 s will be used to identify individuals’ risk of falling [44]. Before testing, the research therapist will demonstrate the tasks.

The 10-Meter Walk test (10MWT) is used to evaluate walking speed, and the results of this test correlate with functional efficiency in older people [45]. The test will be considered complete once the participant crosses the 10-m mark, which will be indicated by adhesive tape on the floor. Two attempts will be allowed, with the first being used to determine a relaxed gait speed, and the second the fastest possible, but safe, speed.

The Back Stretch (BS) test is used to assess flexibility of the upper limbs [46]. It will be carried out in a standing position. The participants will be directed to take one hand up and over the shoulder and reach down the back, and the other hand behind and reaching up the back, with the intention of meeting the hands in the middle of the back, between the shoulder blades. Flexibility will be determined as the distance (in centimeters) between the middle fingers.

The Chair Sit and Reach (CSR) test is used to assess flexibility of the lower limbs [47]. From the sitting position (in a chair), the participant will be directed to use two hands (one on top of the other) to reach forward towards the flexed toes of the extended leg (keeping the other bent for stability). Flexibility will be determined as the distance (in centimeters) between the toes on the flexed foot of the extended leg and the fingers of the hands.

Grip Strength (GS) will be assessed using a dynamometer (JAMAR PLUS + Hydraulic Hand Dynamometer, Patterson Medical). Grip force is strongly correlated with level of independence in the performance of activities of daily living and cognitive abilities of older people [48]. The test will be conducted in a sitting position with the adducted arm to the torso and elbow flexion elbow to 90°. The participant will be instructed to shake the dynamometer grip as hard as possible and keep this consistent for 3–5 s. The test will be repeated three times, and the final measurement will be the average of the three results, in kilograms-force.

The Berg Balance Scale (BBS) has been developed to evaluate the risk of falls in the senior population [49]. The test evaluates static and dynamic balance across 14 tasks. Each task will be assessed on a scale of 0 to 4, where 0 indicates a complete inability to perform a task and 4 the ability to independently performance a task. A maximum score of 56 points is possible. When the task is complete, the participant will be classified into one of four groups, indicating the degree of fall risk.

### Other outcomes

Static balance will be clinically assessed using the CQ-stab stabilometric platform. The board platform will be set up in parallel, 2 m from the walls of the room, where a tag will be placed to focus vision with open eyes during the trials. The measuring device will be calibrated before each test. The study will consist of two 30-s trials performed with open and closed eyes. The participant will be asked to conduct the test without shoes, in a relaxed standing position, with arms down by the sides.

Statistical analyses will be used to assess the results of parameters describing the COP (center of pressure of the feet) for measurements with eyes open and closed. The following will be assessed:SP – length of path of the statokinesiogram calculated for both axes. It defines the path of the COP during the 30-s sample, given in millimetersSPAP – antero-posterior length of COP path, in millimetersSPML – medio-lateral length of COP path, in millimetersMA – mean amplitude of COP from point 0 (radius), in millimetersMAAP – mean antero-posterior amplitude of COP from point 0, in millimetersMAML – mean medio-lateral amplitude of COP from point 0, in millimetersMaxAP – maximal antero-posterior COP projection from point 0, in millimetersMaxML – maximal medio-lateral amplitude of COP from point 0, in millimetersMV – mean velocity of COP projection in millimeters per secondMVAP – mean antero-posterior velocity of COP projection in millimeters per secondMVML – mean medio-lateral velocity of COP projection in millimeters per secondSA – field of COP during the test, in square millimeters

In addition, the examination will be subject to the parameters describing Romberg’s coefficient [50]. The coefficient is defined by the quotient of the values of the parameters measured with eyes open by the parameters measured with eyes closed. These will be:RQSP – Romberg quotient for the length of path of statokinesiogram, which depicts the COP movement during the test in a two-dimensional coordinate systemRQSA – Romberg quotient for COP field marked by the movement of COP in a two-dimensional coordinate systemRQMV – Romberg quotient for the COP means velocity in a two-dimensional coordinate systemRQSPA – Romberg quotient for the COP field quotient to the COP path length

The quality of life assessment questionnaire (SF-36v2) consists of 36 questions and uses an 11-point scale to evaluate functional health and wellbeing, with the final test results providing a psychometric profile of the examined person. Quality of life according to physical health involves an assessment of the following domains: physical functioning – PF, role functioning – RF, body pain – BP, and general health – GH. Quality of life according to mental wellbeing consists of measurements of: vitality – VT, social functioning – SF, emotional role functioning – RE, and mental health – MH. The following domains are also assessed within the scale: health transition – HT, physical component summary – PSC, and mental component summary – MCS [51].

Data will be collected at the following time points: at baseline (before commencement of the intervention), immediately after completion of the intervention, and 12, and 24 weeks after the completion of the intervention.

